### Experimental measures

#### Energy expenditure

Energy expenditure and substrate oxidation rates will be determined from expired gas analysis, at rest and during exercise, using indirect calorimetric methods. The following equations will be used [47]:2$$ Energy\ expenditure\ \left( kcal/\mathit{\min}\right)\kern0.5em =\kern0.5em 3.941\cdot \overset{.}{V}{O}_2+1.106\cdot \overset{.}{V}{CO}_2 $$3$$ CHO- ox\ \left(g/\mathit{\min}\right)\kern0.5em =\kern0.5em 4.344\cdot \overset{.}{V}{CO}_2-3.061\cdot \overset{.}{V}{O}_2 $$4$$ Fat- ox\ \left(g/\mathit{\min}\right)\kern0.5em =\kern0.5em 1.695\cdot \overset{.}{V}{O}_2-1.701\cdot \overset{.}{V}{CO}_2 $$

Pre-exercise REE will be accepted as stable when repeated measurements are within 100 kcal/^.^day [48, 49] and the lowest of these measures will be accepted as RMR [50].

#### Blood sampling

Following the ~ 50 min rest or exercise sessions, a cannula (BD, Venflon™ Pro, Becton Dickenson & Co., Stockholm, Sweden) will be inserted into an antecubital vein from which repeated 10-ml blood samples will be drawn, as previously described. Plasma samples will be centrifuged immediately at 3466 g at 4 °C for 10 min (Heraeus Biofuge Primo R, Kendro Laboratory Products Plc., Tyne and Wear, UK). Serum samples will be left to clot for 60 min at room temperature before centrifugation. All samples will be dispensed into 1.0-ml aliquots and stored at − 80 °C.

### Outcome measures

In order to simplify data analysis and facilitate the interpretation of a complex dataset [51, 52], serial measurements of glucose and insulin responses at baseline, post exercise and in response to the rest/exercise challenge will be converted into simple summary statistics [53], such as incremental area under the curve (iAUC) [54] and insulin sensitivity index (ISIMatsuda) [55]. The Homeostasis Model Assessment (HOMA) calculator, incorporating the updated HOMA-2 model [56], will be used to derive fasting estimates of pancreatic β-cell function, insulin resistance and sensitivity, both at rest and post exercise. A full lipid profile (i.e. triglycerides, total cholesterol, non-esterified fatty acids (NEFA), high-density lipoprotein cholesterol (HDL-C), low-density lipoprotein cholesterol (LDL-C)) will also be assessed to establish the influence of exercise protocol on post-exercise and postprandial responses. From indirect calorimetric measurements, EE, fat and carbohydrate oxidation rates will be determined and compared, primarily during the postprandial phase. The primary and secondary outcome variables are presented in Table 1.

**Table 1 Tab1:** Primary and secondary outcome variables

Outcome measure	Analytical method
Metabolites	
Glucose	Plasma glucose concentration will be assessed using an automated analyser (Randox RX Daytona, Co. Antrim, UK).
Lipids	Serum markers of total triglycerides, total cholesterol, NEFA, HDL-C and LDL-C will also be assessed using an automated analyser and commercially available immunoassays (Randox Laboratories, Co. Antrim, UK).
Hormones	
Insulin	Determined using ELISA (Mercodia AB, Uppsala, Sweden). Variables: (i) incremental area under the curve (iAUC) [54]; (ii) insulin sensitivity index (ISIMatsuda) [55]; (iii) Homeostasis Model Assessment (HOMA-2) model [56]
Inflammatory markers	
Il-6	Baseline and post-exercise measures of IL-6 will be assessed using ELISA (Quantikine HS, R&D Systems Inc., Abingdon, UK)
Energy expenditure	
Total energy expenditure (kcal/min)	Total energy expenditure and substrate oxidation rates will be determined from expired gas analysis, at rest and during exercise, using indirect calorimetric methods, as previously described [47]
CHO-ox (g/min)	
Fat-ox (g/min)	

Abbreviations: *CHO* carbohydrate, *ELISA* enzyme-linked immunosorbent assay, *HDL-C* high-density lipoprotein cholesterol, *IL* interleukin, *LDL-C* low-density lipoprotein cholesterol, *NEFA* non-esterified fatty acids

### Data storage and availability

#### Electronic data records

All electronic files are stored on password-protected computers in rooms 1–48 and 1–50 of the Lois Pope Life Center. Computer security is provided by data encryption, firewall protection, and data backup on the Miami Project server. Source data obtained from metabolic analysis will be entered into a de-identified data bank and stored securely on the network.

#### Physical data records

Data will be stored in a locked room (LPLC 1–50), in a locked file cabinet, which is only accessible to study personnel in the Lois Pope Life Center, [name]. The metabolic analyser used to obtain data is located locked in a room (1–49) accessible by university ID badge after passing a security desk and a hallway accessed by proximity card entry. A security badge is needed to open the office door where the data are stored. A security guard is located in the front lobby, and the hallway to the storage site is secured by proximity card entry.

#### Procedures to release data

To maximise access to the final dataset, after publication of the analyses described within this protocol, we will deposit the final dataset in a to-be-determined data repository. Prior to deposit in the repository, the final dataset will be anonymised. Access to data and procedures to release the data will be defined by the policies of the repository in which the data are placed.

### Power calculation

We plan to recruit 11 male participants with chronic (> 1 year) SCI, by engaging users from the Miami Project to Cure Paralysis community. The primary outcome variables are related to fasting and postprandial glycaemic control, but specifically postprandial insulin area under curve (iAUC). While there are only two previous studies that have compared the effects of MICT and HIIT on biomarkers of metabolic regulation in non-disabled humans [57, 58], both suggest no effect of MICT (vs. CON) and an enhanced effect of HIIT. We therefore hypothesised that there will be no differences in postprandial glycaemic control between CON and MICT and a similarly enhanced effect of HIIT and CRT. Using data from these previous studies, the mean predicted effect size for postprandial iAUC is ~ 1 [57] and for postprandial triglyceride concentrations is 0.97 [59]. We therefore estimated that a final sample size of 11 will be required for this repeated measures study, to provide approximately 90% power to detect a significant difference in ∆ insulin iAUC at an alpha level of 0.05. Recruitment will proceed on a rolling basis until the adequate sample size is reached; emphasis will be placed on considering the demands of the study before enrolling to reduce drop-out during the study.

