**Methods:**

Eleven healthy, chronic SCI (> 1 year, ASIA A-C) men will be recruited. Following preliminary testing, each will complete four experimental conditions, where they will report to the laboratory following an ~ 10-h overnight fast. A venous blood sample will be drawn and expired gases collected to estimate resting metabolic rate (RMR). In order to ensure an isocaloric exercise challenge, each will complete CRT first, with the remaining three conditions presented in randomised order: (1) CRT, ~ 45 min of resistance manoeuvres (weight lifting) interspersed with low-resistance, high-speed arm-crank exercise; (2) CON, seated rest; (3) MICT, ~ 45 min constant arm-crank exercise at a resistance equivalent to 30–40% peak power output (PPO) and; (4) HIIT, ~ 35 min arm-crank exercise with the resistance alternating every 2 min between 10% PPO and 70% PPO. After each ~ 45-min condition, participants will ingest a 2510-kJ liquid test meal (35% fat, 50% carbohydrate, 15% protein). Venous blood and expired gas samples will be collected at the end of exercise and at regular intervals for 120 min post meal.

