### Participants

To address our hypothesis, a cohort of 10 healthy men with chronic SCI, who satisfy the inclusion and exclusion criteria outlined below, will be recruited via advertisement and direct contact with the local SCI community.

Inclusion criteria: (1) Male; (2) Aged ≥ 18 years old; (3) Neurologically stable SCI (ASIA Impairment Scale A-C) at T6 and lower spinal levels for > 1 year; (4) Able and willing to comply with study procedures; (5) Have the ability to understand written and spoken English; and (6) Have the capacity to provide informed consent.

Exclusion criteria: (1) Female; (2) Aged < 18 years; (3) Contraindication to exercise (ACSM Guideline, 10th edition); (4) Lower-extremity fracture or dislocation within 6 months of participation; (5) History of head injury or seizures; (6) Inability to provide informed consent; (7) Restrictions in upper-extremity range of motion that would prevent an individual from achieving an unhindered arm cycling motion or moving throughout a range needed to perform resistance manoeuvres; (8) Had a pressure ulcer at the ischial/gluteus, trochanteric, sacral or heel sites within the last 3 months; (9) Imprisonment in state or federal jail or prison; (10) Taking any medication that might interfere with the study outcomes (this will be reviewed by the research team on a case-by-case basis should a potential participant be on regular medication. The *British National Formulary* will be checked for potential effects that might introduce bias in the study); and (11) Illness/condition that might interact with study measures (e.g. diabetes, heart disease) or pose undue personal risk.

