### Statistical analysis

All data from participants who successfully complete the study will be included in the analysis. The differences in key outcome variables between experimental conditions (CON, MICT, CRT and HIIT) and time (dependent on variable) will be analysed using a two-way (condition × time) fully repeated measures analysis of variance (ANOVA). Where significant interactions are observed, multiple *t* tests will determine the location of variance. Significant post-hoc effects will be subjected to a Holm-Bonferroni stepwise adjustment. Standardised effect sizes (Cohen’s *d*) will also be calculated. This will provide a practical interpretation of the size of the effects of each experimental condition relative to CON. For all the above statistical approaches, statistical significance will be set at an alpha level of *p* ≤ 0.05. We will explore the use of confidence intervals and magnitude-based inferences to assess the clinical significance of the effect.

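### The stated power of about 90% with 11 participants fits neither the small-sample t tests nor the Holm-adjusted comparisons that the plan specifies, and the planned sample size is 10 in one section and 11 in two others

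*Protocol article*

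**What the plan says.** The Power calculation section gives insulin iAUC after the meal as the specific primary variable. It states that "the mean predicted effect size for postprandial iAUC is ~ 1" and that the effect size "for postprandial triglyceride concentrations is 0.97". From these it concludes: "We therefore estimated that a final sample size of 11 will be required for this repeated measures study, to provide approximately 90% power". Alpha is 0.05. The section expects CON and MICT not to differ, and HIIT and CRT to be improved to a similar degree. It does not name the test, its sidedness, the contrast, or the standard deviation that scales the effect.

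The Statistical analysis section plans a condition-by-time repeated measures ANOVA on participants who complete the study. Where the interaction is significant, t tests follow, and then: "Significant post-hoc effects will be subjected to a Holm-Bonferroni stepwise adjustment". The number of contrasts is not given.

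The central hypothesis under Objectives sets HIIT and CRT against MICT and CON, which is four contrasts.

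The Methods part of the abstract says "Eleven healthy, chronic SCI (> 1 year, ASIA A-C) men will be recruited", which agrees with the Power calculation section. The Participants section says "a cohort of 10 healthy men with chronic SCI".

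**The concern.** The power statement describes one comparison at an unadjusted 0.05. The planned analysis compares four conditions by t tests with about 10 degrees of freedom and then adjusts for multiplicity. Small degrees of freedom and adjustment both lower power, and the stated 90% reflects neither. The two sample sizes add a further loss if 10 is the real number.

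What is at stake is how a null result is read. A non-significant HIIT or CRT contrast would be taken as evidence from a trial with 90% power. The Discussion presents this study as groundwork for longer intervention trials, so a false null here could mislead that next step.

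**Working it through.** **Inputs.** n = 11 (Power calculation, abstract) or 10 (Participants); effect about 1; alpha 0.05; pattern CON = MICT and HIIT = CRT (all from Power calculation); t tests and Holm-Bonferroni (Statistical analysis). Assumptions added here: two-sided testing and, except in step 5, an effect of 1 standard deviation of the paired differences.

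**1. Reproducing the plan's figure.** Two-sided normal approximation for a paired comparison:
- n = ((1.960 + 1.282) / 1)² = 10.51, rounded up to 11.
- Power at 11 = Φ(1 × √11 − 1.960) = Φ(1.357) = 91.3%.

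A contrast using the pooled error of a four-condition repeated measures ANOVA has (4 − 1)(11 − 1) = 30 degrees of freedom, critical value 2.042 and noncentrality √11 = 3.317. Power is 89.4%. Both routes agree with the stated figure.

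**2. Exact two-sided paired t test.** Power = P(|T| > t(0.975, n − 1)), with T noncentral t on n − 1 degrees of freedom and noncentrality √n.

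| n | Power |
|---|---|
| 10 | 80.3% |
| 11 | about 85% |
| 12 | 88.3% |
| 13 | 91.1% |

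Thirteen completers are needed to pass 90%. The normal approximation is optimistic because it treats the standard deviation as known.

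**3. Sensitivity to the approximate effect.** At n = 11 the exact two-sided paired t test gives 82.6% for 0.97, 88.0% for 1.05 and 90.7% for 1.10.

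**4. After Holm adjustment.** Simulation with 100,000 runs, equal within-person correlations, means 0, 0, 1, 1 for CON, MICT, HIIT, CRT in units of the standard deviation of differences, and separate paired t tests. The ANOVA gate before the t tests is not simulated; it cannot raise these figures.

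| Family adjusted | Per true contrast, n = 11 | Per true contrast, n = 10 |
|---|---|---|
| Six pairwise | about 61% | about 53% |
| Three against CON | about 71% | about 65% |
| Four HIIT/CRT versus MICT/CON | about 75% | about 68% |

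The chance that all four hypothesis contrasts are significant at n = 11 is about 31% with the six-contrast family, about 55% with the four-contrast family, and about 60% with no adjustment. Whatever the family, Holm can only remove significance, so the unadjusted 85% is a ceiling for these paired t tests.

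**5. If the effect of 1 is on the between-subject scale.** The paired effect is then 1 / √(2(1 − ρ)), where ρ is the within-person correlation, which the protocol does not give. Unadjusted power at n = 11:
- ρ = 0.3: paired effect 0.845, power 71%.
- ρ = 0.5: paired effect 1.000, power 85%.
- ρ = 0.7: paired effect 1.291, power 97%.

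**The case against.** The strongest reply is that the stated figure is reproducible. The usual normal approximation gives both the 11 and the 90%, a pooled-error contrast gives 89.4%, and the protocol does not say which test was used. A reader might infer that only a one-sided test (92.4% at 11) could yield the claim, or that the sum was done wrongly. The documents do not support either inference. The gap comes from the choice of method.

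The first planned test is also an ANOVA. Reduced to one summary value per condition, with the assumed pattern, the omnibus F test has noncentrality 11 × 1 / 0.5 = 22 and power of about 97% at n = 11. That stands, but an omnibus result does not say which exercise mode differs from which, and the hypothesis is about that.

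The inputs are approximate as well: an effect of 1.10 gives 90.7% by the exact test, and a between-subject scale with high correlation gives more than 90%. This too stands, and it is why 85% must be tied to a paired difference of exactly 1.

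Finally, a reader might take 61% as the trial's real power. That figure needs a six-contrast family, which the protocol does not state, and the power statement never claimed power after adjustment. The number of contrasts may be left to a fuller document. What remains is that the adjusted power is below the stated figure under each family examined.

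**Conclusion.** The concern holds in this form: the 90% is obtainable by approximation or by pooling error across conditions, but the paired t tests that would locate the differences do not deliver it at an effect of 1. On a two-sided exact test, unadjusted power is about 85% with 11 completers and 80% with 10. Adjusted power per true contrast at 11 is about 61% to 75%, depending on the family.

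These figures assume two-sided testing, a paired standardised difference of 1.0, equal correlations, and the protocol's own pattern of effects. If the effect is scaled by the between-subject standard deviation, unadjusted power could be anywhere from about 71% to 97% for correlations of 0.3 to 0.7, so the missing standardiser matters as much as the choice of test.

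The contradiction between 10 and 11 is plain text against text and depends on none of these assumptions. It also bears on dropout: 11 is both the number to recruit and the final number required, and only completers are analysed, so a single withdrawal leaves 10.

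**What to change.** 1. Restate the power along these lines: about 85% power with 11 completers, for a two-sided paired t test at 0.05, a standardised paired difference of 1.0, and one named contrast on insulin iAUC, without adjustment. If another test or standardiser was used, name it and give the within-person correlation where it is needed.
2. Declare the family of contrasts to which Holm-Bonferroni applies and give the power after adjustment. If the family is the four HIIT/CRT versus MICT/CON contrasts, this is about 75% per contrast.
3. Replace 10 and 11 by one planned number in the abstract, Participants and Power calculation sections, and say whether it means recruited or completing.

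The Holm strategy itself need not change. A fixed testing sequence on HIIT alone would protect the first comparison but would leave CRT, half of the central hypothesis, outside it, so it is not proposed here.

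The Trial status section shows that recruitment has ended, so the change is to wording only. It adds no participants; the cost is a less favourable stated power.

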### Statistical analysis

All data from participants who successfully complete the study will be included in the analysis. The differences in key outcome variables between experimental conditions (CON, MICT, CRT and HIIT) and time (dependent on variable) will be analysed using a two-way (condition × time) fully repeated measures analysis of variance (ANOVA). Where significant interactions are observed, multiple *t* tests will determine the location of variance. Significant post-hoc effects will be subjected to a Holm-Bonferroni stepwise adjustment. Standardised effect sizes (Cohen’s *d*) will also be calculated. This will provide a practical interpretation of the size of the effects of each experimental condition relative to CON. For all the above statistical approaches, statistical significance will be set at an alpha level of *p* ≤ 0.05. We will explore the use of confidence intervals and magnitude-based inferences to assess the clinical significance of the effect.

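### Restricting the analysis to men who finish all four conditions, with a complete-row ANOVA, discards usable visits from anyone who misses one

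*Protocol article*

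**What the plan says.** Only the protocol article is at hand. Its Statistical analysis section fixes two things.

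- The analysis set: "All data from participants who successfully complete the study will be included in the analysis". No other set is given, and what counts as successful completion is not defined.
- The method: a two-way "fully repeated measures analysis of variance (ANOVA") with condition and time as factors, followed by t tests where the interaction is significant.

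The Power calculation section adds: "We therefore estimated that a final sample size of 11 will be required for this repeated measures study". On enrolment it says: "Recruitment will proceed on a rolling basis until the adequate sample size is reached". It gives no drop-out rate. The only provision is that "emphasis will be placed on considering the demands of the study before enrolling to reduce drop-out during the study".

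Other sections make partial data foreseeable. Participants may withdraw whenever they wish (Recruitment), and exercise sessions are stopped on listed symptoms (Emergencies and adverse events). CRT always comes first, and CON, MICT and HIIT follow in random order (Study design).

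**The concern.** The analysis set and the model point the same way: a participant contributes all four conditions or nothing. Someone who provides CRT, CON and MICT but not HIIT has complete data for three of the six pairwise comparisons (CRT–CON, CRT–MICT, MICT–CON), yet is removed from all six. Because CRT is always first, anyone who leaves during the later visits has already given a CRT session that is then thrown away. With a target of 11, each such loss is noticeable.

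Missed or stopped sessions are also plausibly related to condition. The symptoms that stop a session are more likely during hard arm-cranking than during seated rest. If men who do not finish are left out and others are enrolled until 11 have finished, the analysed group is selected for tolerating every condition.

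**Working it through.** **1. The plan's own figure.** Inputs from Power calculation: effect size about 1 for insulin iAUC (read here as the mean paired difference over its SD, dz, because the standardiser is not stated), alpha 0.05 (taken as two-sided), power about 90%.

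- Normal approximation: n = ((1.960 + 1.282)/1)² = 10.51, rounded up to 11.
- Power at 11: Φ(√11 − 1.960) = Φ(1.357) = 91.3%. The stated 11 and roughly 90% are reproduced.
- The two-sided paired t test (noncentral t, noncentrality dz·√n, n − 1 degrees of freedom) gives 84.8% at n = 11, 80.3% at n = 10 and 74.8% at n = 9.

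**2. Non-completers not replaced.** Assume 2 of 11 men miss only HIIT. Completers-only leaves 9 men for every contrast. With all available visits:

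- Contrasts among CRT, CON and MICT have all 11 men.
- For HIIT–CON, take four conditions with equal variance and common within-person correlation r (compound symmetry, variance components treated as known). In units of the outcome variance, the generalised least squares variance is A/9 + B/11, where A = (1 − r)(1 + 3r)/(1 + 2r) is the variance of HIIT given the other three conditions and B = (1 − r)(1 + r)/(1 + 2r). These sum to 2(1 − r), the variance of a paired difference.
- Effective n = 2(1 − r)/(A/9 + B/11) = 2(1 + 2r)/[(1 + 3r)/9 + (1 + r)/11].

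| r | Calculation | Effective n, HIIT–CON |
|---|---|---|
| 0.3 | 3.2/(0.2111 + 0.1182) | 9.7 |
| 0.5 | 4.0/(0.2778 + 0.1364) | 9.7 |
| 0.9 | 5.6/(0.4111 + 0.1727) | 9.6 |

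So about a third of the loss is recovered for HIIT–CON (0.6 to 0.7 of 2 men), and all of it for contrasts without HIIT.

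**3. Non-completers replaced.** Here n stays at 11. Enrolment needed for 11 completers is 11/(1 − d), rounded up. With assumed losses d:

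- 10%: 12.2, so 13 enrolled and 2 left out
- 20%: 13.75, so 14 enrolled and 3 left out
- 30%: 15.7, so 16 enrolled and 5 left out

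Suppose a share p with the lowest tolerance is lost, and tolerance correlates ρ with the individual HIIT–CON effect. The completers' mean then shifts by ρ·φ(a)/(1 − p), with a = Φ⁻¹(p), in SDs of the paired difference.

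| Loss p | ρ = 0 | ρ = 0.3 | ρ = 0.5 |
|---|---|---|---|
| 10% | 0 | 0.06 | 0.10 |
| 20% | 0 | 0.11 | 0.18 |
| 30% | 0 | 0.15 | 0.25 |

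Both p and ρ are assumptions; the article supplies neither.

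**The case against.** Four points can be made for the plan.

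- **Replacement is not stated.** A reader might infer from the rolling recruitment to a final 11 that men who fail a condition are discarded and replaced. That is a fair inference and nothing contradicts it, but no sentence says so. This stands.
- **Bias is not shown.** A reader might go further and conclude that the estimates are biased toward men who tolerate hard exercise. All contrasts are within person, so selection on tolerance shifts them only if tolerance is related to the individual effect. The article gives no basis for the size or direction of that relation. This stands.
- **Selection is largely built in at entry.** Every man does a HIIT familiarisation session at the same work intensity, and randomisation comes only after that session and CRT. Inclusion requires ability and willingness to comply, and payment follows completion of all assessments. Many men who cannot tolerate the intervals would be identified early, and no analysis model removes that selection. This also stands, and it limits what the change can achieve. It does not justify discarding visits that were made.
- **The power loss is conditional and only partly recoverable.** A fall from 84.8% to 74.8% at n = 9 applies only if two men are lost and not replaced, so it cannot be added to the replacement problem. A man with no HIIT visit has no HIIT outcome under any model, which is why the gain for HIIT–CON is small.

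It cannot be answered that the matter was simply left to an analysis plan, because the article itself states the analysis set and the model.

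**Conclusion.** The point holds as one of wasted data. Under the stated set and the classical form of the stated ANOVA, anyone who misses one condition loses all his other visits, and this needs no assumption about why he missed it. Whether a man with a stopped session is treated the same way depends on the undefined term for completion; on the natural reading he is.

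The size depends on attrition that the article does not give. In the illustration (2 of 11 missing only HIIT, no replacement, compound symmetry), an all-visits analysis raises effective n from 9 to 11 for contrasts without HIIT and to about 9.6 to 9.7 for HIIT–CON. The gain on HIIT–CON is real but modest.

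The documents do not support saying that non-completers are replaced, that the effects are biased, or that the trial has lost 10 points of power. If replacement does occur, it selects further for tolerance; under the assumed ranges the shift runs from 0 to 0.25 SD of the paired difference, direction unknown. This is worth correcting and does not invalidate the design.

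**What to change.** - **Main analysis.** Use a linear mixed model fitted by restricted maximum likelihood, with condition and time (where the outcome is serial) as fixed effects, participant as random effect, and small-sample degrees of freedom such as Kenward–Roger. Include every available condition visit from all participants with at least one evaluable main-trial condition. CRT must count: a set defined by randomised visits alone would drop men who gave only the CRT session.
- **Sensitivity analysis.** Keep the completers-only ANOVA, and define in advance what counts as having completed a condition.
- **Reporting.** Give the number of missed or stopped sessions and the reasons, by condition, and state whether any participant was replaced.

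The cost is a change of wording and a little more programming, with no new participants or measurements, so the closed recruitment is no obstacle. With complete, balanced data and a matching covariance structure, the result is essentially that of the ANOVA, so little is given up if nobody misses a visit. The model relies on missing at random. That can fail if men miss HIIT for reasons tied to their unobserved response to it, but it is less restrictive than what an unbiased completers-only analysis generally needs.

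### The plan would explore magnitude-based inference outside its error control, and its committed tests cannot support the predicted absence of a CON–MICT difference or the similarity of HIIT and CRT

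*Protocol article*

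**What the plan says.** The Statistical analysis section of the protocol article fixes a condition × time repeated-measures ANOVA, t tests where the interaction is significant, a Holm-Bonferroni adjustment of those t tests, and significance at p ≤ 0.05 for the approaches listed up to that point. Cohen's d is to give a practical reading of "the size of the effects of each experimental condition relative to CON". The section then closes with: "We will explore the use of confidence intervals and magnitude-based inferences to assess the clinical significance of the effect". It gives no smallest worthwhile effect, probability threshold or labelling rule.

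The Objectives section states the central hypotheses as superiority: HIIT and CRT are expected to improve on MICT or CON. The Power calculation adds the prediction that "there will be no differences in postprandial glycaemic control between CON and MICT and a similarly enhanced effect of HIIT and CRT". The sample size itself is set to "detect a significant difference in ∆ insulin iAUC at an alpha level of 0.05". No equivalence margin appears in the article.

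**The concern.** Two separate weaknesses lie in how results will be interpreted.

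First, magnitude-based inference turns a small-sample interval into verbal labels such as 'possibly' or 'likely' beneficial. It is named after the sentence that sets alpha, and the Holm adjustment applies only to the t tests. A contrast that fails the controlled test could therefore still receive a favourable label from a method whose rule has not been fixed.

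Second, two of the predictions are predictions of sameness: CON with MICT, and HIIT with CRT. The committed tools look only for differences. With 11 men a non-significant result is likely even if moderate exercise has a real, moderate effect, and that result would appear to match the prediction. What is at stake is a report that moderate exercise does nothing, or that the two intense modes are interchangeable, when the data are merely imprecise.

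**Working it through.** **Inputs.** From the Power calculation: N = 11, alpha 0.05, power about 90%, effect size about 1 for insulin iAUC. Assumed, because the article does not give them: two-sided testing; a smallest worthwhile change of 0.2 between-person SD; a within-person correlation ρ of 0.5, 0.7 or 0.9; and the usual labelling rules given in step 2.

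**1. The plan's own figure.** The paired normal approximation gives n = ((1.960 + 1.282)/1)² = 10.51, rounded up to 11, with power 91.3% at 11. The stated size is reproduced (the exact two-sided paired t test gives 84.8%). This is power to find a difference of one SD of the paired differences. It says nothing about showing sameness.

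**2. Labels given to null trials.** With between-person SD 1, the SD of a paired difference is √(2(1 − ρ)), that is 1.00, 0.77 and 0.45 at ρ = 0.5, 0.7 and 0.9. Null trials with n = 11 were simulated. For each, the chances of benefit (above +0.2) and harm (below −0.2) were read from the t distribution with 10 degrees of freedom.

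- Non-clinical rule: chance of harm under 5%; 'possibly' needs a chance of benefit above 25%, 'likely' above 75%.
- Clinical rule: chance of harm under 0.5% and chance of benefit above 25%.

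Share of all null trials that are non-significant on the paired t test and also labelled beneficial:

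| Label | ρ = 0.5 | ρ = 0.7 | ρ = 0.9 |
|---|---|---|---|
| Non-clinical, at least 'possibly' | 13% | 17% | 17% |
| Non-clinical, 'likely' or more | 6.5% | 4.0% | 0.2% |
| Clinical, beneficial | 0.2% | 0.8% | 4.8% |

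**3. Precision for the predictions of sameness.** The 95% CI half-width for a paired contrast is t(0.975, 10)/√11 = 2.228/3.317 = 0.67 SD of the differences. An observed difference of exactly zero would still leave an interval of about ±0.67.

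**4. Chance of non-significance when an effect exists.** Unadjusted two-sided paired t test, n = 11, noncentrality d√11, with d in SDs of the paired differences:

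- d = 0.2: 91% non-significant
- d = 0.5: 68%
- d = 0.8: 33%

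The scale matters. If 0.5 is in between-person SDs, then d = 0.5/√(2(1 − ρ)) = 0.50, 0.65 and 1.12, and the chance of non-significance is 68%, 51% and 8% at ρ = 0.5, 0.7 and 0.9.

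**5. Would a formal equivalence test help?** Two one-sided tests at 5% each, true difference zero, n = 11: power is about 0%, 8%, 59% and 85% for assumed margins of 0.2, 0.5, 0.8 and 1.0 SD of the differences. Only a margin as large as the effect the trial hopes to detect would give reasonable power.

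**The case against.** The strongest reply is that the article commits to far less than a reader might infer.

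- **Adoption.** A reader might conclude that magnitude-based inference is the adopted way of interpreting effects while confidence intervals are left optional. The text does not support that. One verb, 'explore', governs both, and the committed analysis is ANOVA, adjusted t tests and Cohen's d. Nothing lets the labels replace the p-value on the primary outcome. This stands, and it limits the point to a proposed extra route.
- **Size.** A reader might cite the 30–39% of null trials that receive some 'possibly' or stronger label under the non-clinical rule. That figure counts both directions and includes trials that are already significant, so it does not measure null results turned into benefits. The smaller figures in the table do.
- **Sameness.** A reader might say that the plan has no means at all of addressing CON against MICT, or that it will report non-significance as equivalence. The article says neither. Confidence intervals, if used, would bear on the question, and the central hypotheses are superiority hypotheses. What remains is that no committed tool can support the prediction.
- **Contrasts with MICT.** These are not missing, because the post-hoc t tests cover all four conditions. Only the Cohen's d sentence is confined to comparisons with CON.
- **Scope.** A margin, a smallest worthwhile effect and reporting formats may sit in an analysis plan that is not shown. Their absence is therefore not the point. Naming magnitude-based inference is a choice made in this document, and a better method can replace it at once.

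**Conclusion.** The point holds as a cheap improvement, not as a flaw that invalidates the trial. Exploring magnitude-based inference would add a route to favourable wording outside the stated alpha and Holm control. Its size depends on the rule, which the article does not state. At the level of 'possibly', about one null trial in six to eight would be non-significant yet labelled beneficial. At 'likely' or more, or under the clinical rule, the share runs from 0.2% to 6.5%. These figures rest on the assumed 0.2 SD threshold and correlations of 0.5 to 0.9.

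The second part is firmer. The half-width of 0.67 SD of the paired differences follows from n = 11 alone, so the committed tests cannot support the predicted sameness of CON and MICT or of HIIT and CRT. How often a real effect of 0.5 SD would be missed depends on the SD scale: 68% in SDs of the differences, and between 8% and 68% in between-person SDs over the same correlations.

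**What to change.** In the Statistical analysis section:

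1. Delete magnitude-based inference.
2. Commit to mean paired differences with 95% confidence intervals for each contrast in the hypotheses, including HIIT and CRT against MICT as well as against CON.
3. State that a non-significant CON–MICT or HIIT–CRT result will not be reported as no difference or similarity, and that the conclusion will be drawn from the effects the confidence interval excludes.

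This takes two or three sentences and needs no further participants or data. Recruitment had already ended according to the Trial status section, but these are analysis and reporting rules and can still be changed; the change should be dated. The price is fewer favourable verbal labels and a weaker statement about the predicted null, which is all that 11 men can support.
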